## Abstract

**Background:**

The benefits of mother’s own milk (MOM) for preterm infants have been widely recognized. Many studies have shown that the rate of breastfeeding of premature infants remains very low. Although many studies use measures to promote breastfeeding, few high-quality cluster randomized controlled studies have evaluated the effectiveness of these measures. WeChat is an instant messaging software for smart terminals, and WeChat mini-programs have been widely used to promote health and self-management in China. Based on this background, we designed a randomized controlled study based on WeChat mini-programs to promote MOM feeding of premature infants in the neonatal intensive care unit (NICU).

**Methods/design:**

This study will evaluate the effectiveness of WeChat mini-programs to increase the consumption of MOM feeding in twelve NICUs in Jiangsu Province, namely, six “intervention” NICUs and six “control” NICUs. The study process is as follows: (1) design and preparation, (2) NICU recruitment and training, (3) interpretation and analysis of baseline data, (4) quality control implementation process, and (5) data analysis feedback and publication of study reports. The primary outcome is the proportion of MOM feeding of premature infants during NICU hospitalization. The secondary outcomes are as follows: (1) time to initiation of MOM feeding (hours) and proportion of first-time MOM feeding (%), (2) duration of parenteral nutrition (days), (3) time to total gastrointestinal feeding (days), (4) hospitalization time and hospitalization cost, and (5) incidence of complications (necrotizing enterocolitis, bronchopulmonary dysplasia, feeding intolerance, late-onset sepsis, retinopathy of prematurity).

**Discussion:**

This study is the first cluster randomized controlled trial on the intervention of using a WeChat mini-program-based lactation consultant for premature infants in the NICU in China. We hope this study can improve the consumption of MOM by NICU premature infants during hospitalization through the intervention of WeChat mini-programs.

**Trial registration:**

ClinicalTrials.gov NCT04383379. Registered on May 5, 2020.

**Supplementary Information:**

The online version contains supplementary material available at 10.1186/s13063-021-05731-6.

## Background

The benefits of breastfeeding for preterm infants have been widely recognized, especially mother’s own milk (MOM) feeding, because it can not only reduce the incidence of preterm infant complications, such as retinopathy of prematurity (ROP) [1], necrotizing enterocolitis (NEC) [2, 3], infection [4, 5], and bronchopulmonary dysplasia (BPD) [6], but also improve the development of the nervous system [7] and health status in adulthood [8].

In recent years, with the increasing prevalence of prenatal lactation consultation, breastfeeding education, and guidance, mothers of preterm infants have greatly improved their understanding of breastfeeding worldwide. However, a large gap persists in different regions and neonatal intensive care units (NICUs) for MOM feeding of preterm infants, which may be due to closed management practices at most NICUs in China and the prohibition of parents in the NICU ward. In each NICU, the measures of feeding and other factors are related because they can directly affect the volume of breast milk expression of preterm mothers and whether preterm infants can accept MOM feeding. The American Academy of Paediatrics (AAP) suggests that premature infants should be breastfed as early as possible, and many hospitals have developed strategies to promote breastfeeding. The US Centers for Disease Control and Prevention (CDC) has suggested that breastfeeding should be promoted by professional institutions. MOM is considered the gold standard nutrition for NICU premature infants [9]. A multicentre study [10] reported that in China, only 23% of premature infants in the NICU receive MOM feeding during hospitalization, and this is only partial MOM feeding rather than exclusive MOM feeding. In 2020, an early postpartum breastfeeding rate goal of 75% was set for healthy women [11], but the growth of the breastfeeding rate is very low or even stagnant [12].

Although many studies have been conducted to promote exclusive breastfeeding interventions, few high-quality randomized controlled trials have been performed. Breastfeeding interventions have been demonstrated to be effective in improving the rate of exclusive breastfeeding, especially individualized interventions related to the promotion of breastfeeding [13]. The success of breastfeeding is influenced by socioeconomic, cultural and personal factors (maternal age, disease, delivery mode, premature status), and other factors, which mainly depend on breastfeeding education and support provided by medical professionals [14–16].

In recent years, the number of smartphone users has increased, and some devices will be an important part of health promotion and self-management [17]. Currently, many breastfeeding applications have been used in the clinic to help new mothers understand breastfeeding and provide breastfeeding guidance after discharge [18]. In 2019, an app called “Milk Man” developed in Australia, which can record breastfeeding information and provide support for fathers and expectant fathers to prepare for breastfeeding throughout the perinatal period, showed strong applicability and good effect with game-form forum communication [19]. WeChat is an instant messaging software for smart terminals launched by Tencent on January 21, 2011. It can provide users with chat and WeChat payment capabilities, circles of friends, public platforms, WeChat mini-programs, and other functions. Its users cover more than 200 countries and more than 20 languages. WeChat is widely used by people of different ages, cultural backgrounds, and industries. There are 1.15 billion monthly active users (2019, 11, 3), and it is one of the most popular social platforms in China. More than 300 million WeChat mini-programs are used every month [20]. WeChat mini-programs are applications that can be used without downloading and installation and can meet the needs of different people and industries. In the era of WeChat mini-programs, users only need to scan or search to use them, making these programs convenient and efficient.

Based on this background, we designed a lactation consultant intervention based on the WeChat mini-programs to promote the MOM feeding of premature infants in the NICU. To further improve the quality of the intervention, we have planned a cluster randomized controlled trial. Using the WeChat mini-program as a lactation consultant, we can improve the lactation of premature mothers such that premature infants can receive MOM feeding as soon as possible during hospitalization in the NICU to improve the prognosis of premature infants. If this program is successfully implemented and proven effective, it can be promoted in other NICUs in China.

## Methods/design

### Study objectives

The primary objective of the study is to evaluate the effectiveness of using the “Ning BX breastfeeding” WeChat mini-program lactation consultation intervention for improving the proportion of MOM feeding of premature infants during hospitalization in the NICU.

The secondary objective of this study is to explore the other related effects of the intervention on MOM feeding of premature infants: (1) to shorten the time for premature infants to receive mother’s milk for the first time and increase the proportion of first-time MOM feeding; (2) to shorten the duration of parenteral nutrition and achieve full enteral gastrointestinal feeding as soon as possible; (3) to shorten the hospitalization time and reduce the hospitalization cost; and (4) to reduce the incidence of premature complications, such as necrotizing enterocolitis (NEC), bronchopulmonary dysplasia (BPD), late-onset sepsis (LOS), and retinopathy of prematurity (ROP).

### Study design

In this study, a cluster randomized controlled matching design will be used. This protocol follows the 2013 SPIRIT guidelines (Additional file 1), and the hospital has been chosen as a cluster. The supervision unit will be used for quality control, coordination and technical support during the entire study. In this study, we will recruit 12 NICUs. The two NICUs with a similar number of premature infants, the same NICU scale, and the same range of MOM feeding proportion taken as a floor will then randomly be divided into two groups, namely, an intervention group of 6 NICUs and a control group of 6 NICUs. In the intervention group, only the guardian of premature infants used the “Ning BX breastfeeding” WeChat mini-programs, and other treatments were the same as those in the control group. The guardian could choose to withdraw at any time, which does not affect any treatment of premature infants. The control group will receive only routine management. Flowcharts of the study design and timeline are provided in Figs. 1 and 2, respectively.

**Fig. 1 Fig1:**
[figure not shown]
Study protocol flowchart of MOM feeding lactation consultant intervention via WeChat mini-programs

**Fig. 2 Fig2:**
[figure not shown]
Schedule of enrolment, interventions, and assessments

### Hypothesis

We hypothesize that if the “Ning BX breastfeeding” WeChat mini-programs are implemented successfully, the proportion of MOM feeding of premature infants during hospitalization in the NICU will increase by at least 15%; the second hypothesis is that the length of hospitalization and medical expenses will be reduced, and the quality of life of the premature infants will be improved.

### Eligibility and exclusion criteria

#### Inclusion criteria

Preterm infants weighing less than 2000 g and/or with a gestational age of less than 34 weeks.The guardians of all preterm infants will provide informed consent.

#### Exclusion criteria

Pregnancy with serious diseases (such as malignant tumour, epilepsy or heart dysfunction), infectious diseases, or other medical contraindications for breastfeeding (such as galactosemia);No parental consent.

### Randomization

Because the intervention cannot be completely blinded in this study due to the randomization of groups as units and differences in NICU scale, a whole-group matching design will be adopted. Twelve units will be randomized into two groups (intervention and control groups) instead of patient randomization to avoid the confounding effect of patients in the control groups. Two NICUs with a similar number of premature infants, the same NICU scale, and approximately the same range of MOM feeding taken as a floor will be randomly divided into six groups. Next, the names of 12 units will be written on paper and placed in the same envelope. One third-party individual blinded to this project will take one envelope from each of the six groups, and the six chosen envelopes will be assigned to the intervention group. The remaining six envelopes will be assigned to the control group.

### Sample size calculation

The proposed sample size is based on the primary outcome of the proportion of MOM feeding. According to the baseline data reported (unpublished data) by each unit in 2019, the average proportion of MOM feeding was 42.46%. We expect the proportion of MOM feeding of premature infants during NICU hospitalization to increase by at least 15% in the intervention group compared with that in the control group. We will achieve 90% power to detect a difference between the group means of at least 6, and the standard deviation of subjects is 30.00, assuming the intracluster correlation coefficient is 0.005 [21, 22]. We estimate a total sample size of 1620 (810 in the intervention group and an average of 135 in each group). Considering a 10% drop-out rate following enrolment in the study, we will enrol 900 premature infants in the intervention and control groups. To achieve this sample size, we will conduct a 1-year study in 12 NICUs.

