### Statistical analysis

Statistical analysis will be performed by statisticians; continuous variables will be presented as the means and standard deviations, and categorical variables will be presented as numbers and proportions. Adjusted chi-square analysis will be performed to compare the primary outcome indicators of the intervention and control groups, and the cluster effect will be considered. The two-level stratified logistic regression model will be used to compare the main outcome indicators between the two groups.

Superiority test will be used if necessary. The results will be adjusted based on an evaluation of neonatal characteristics (such as gestational age, small for gestational age, gender, and 5-min Apgar score) and NICU characteristics (number of preterm infants admitted and rate of MOM feeding). All statistical tests will be two-tailed, and *P* < 0.05 will be considered significant.

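### The stated 90% power does not follow from the stated inputs: they give about 88% on a normal approximation and about 80% once inference rests on 12 clusters

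*Protocol article*

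**What the plan says.** All the inputs are printed in the protocol article.

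- **Sample size calculation:** the claim is "We will achieve 90% power to detect a difference between the group means of at least 6". For the spread, "the standard deviation of subjects is 30.00", and the clustering term is set by "assuming the intracluster correlation coefficient is 0.005".
- **Sample size calculation, result:** "We estimate a total sample size of 1620 (810 in the intervention group and an average of 135 in each group". Since 810/6 = 135, the last figure is the average per NICU. Enrolment is then raised to 900 per arm to cover 10% drop-out.
- **Study design:** "an intervention group of 6 NICUs and a control group of 6 NICUs", formed from matched pairs.
- **Statistical analysis:** "All statistical tests will be two-tailed", at the 5% level. A cluster-adjusted chi-square and a two-level model are planned.
- **Randomization:** matching is justified partly by "differences in NICU scale".

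The article names no sample size formula or software and mentions no allowance for the small number of clusters.

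**The concern.** The difference, SD, ICC, cluster size, number of clusters and significance level are all given, so the power can be recomputed, and it does not come to 90%. There are two separate gaps. One is arithmetic: even the most generous standard calculation for a two-sided test falls short. The other is larger and concerns method: with 12 randomised units, between-NICU variance is estimated from few units, and normal critical values overstate the power.

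The stake is how a non-significant primary result would be read. The stated power implies a 10% chance of missing a true 6-point difference. The printed inputs imply about 12% on the normal approximation and about 20% on 10 degrees of freedom. The article ties wider adoption of the programme to success here, so that risk should be stated correctly.

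**Working it through.** **Inputs.** Difference d = 6, SD = 30 (variance 900), ICC = 0.005, m = 135 evaluable infants per NICU and claimed power 90% (Sample size calculation); 6 NICUs per arm (Study design); two-sided alpha 0.05 (Statistical analysis).

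**1. Sample size for 90% power, ignoring clustering.** n = 2 × (1.960 + 1.2816)² × 900/36 = 525.4 per arm.

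**2. Allowing for clustering.** Design effect = 1 + (135 − 1) × 0.005 = 1.67. The need at that cluster size is 525.4 × 1.67 = 877 per arm, against 810 planned. With the number of NICUs fixed at 6 per arm, the cluster size solves to

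m = 525.4 × (1 − 0.005) / (6 − 525.4 × 0.005) = 155.0,

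which is 930 per arm and 1,860 in total.

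**3. Power at the planned size.** Effective n = 810/1.67 = 485.0 per arm. Standard error = 30 × √(2/485.0) = 1.926. Standardised difference = 6/1.926 = 3.115.

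- Normal approximation: Φ(3.115 − 1.960) = 87.6%.
- Noncentral t, 12 − 2 = 10 df, noncentrality 3.115: 80.1%. Simulating NICU means (200,000 runs) gave 80.2%.

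The t version reaches 90% for 6 points only at about 235 infants per NICU (2,820 in total).

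**4. Difference detectable with 90% power on 10 df.** (2.228 + 1.372) × 1.926 = 6.9, or about 7 points. The normal approximation gives (1.960 + 1.2816) × 1.926 = 6.24 points.

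**5. Inputs that would reproduce the printed 135.** Both keep the normal approximation.

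- ICC 0.004, difference 6: m = 525.4 × 0.996 / (6 − 525.4 × 0.004) = 134.2, which rounds up to 135. Power at 135 is 90.1%.
- ICC 0.005, difference about 6.24: m is about 135 and power 90.0%. Such a difference could have been printed as 6.

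**6. Other readings of the plan.**

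| Variant | Normal | t, 10 df |
|---|---|---|
| As stated: 135 per NICU, difference 6 | 87.6% | 80.1% |
| All 900 per arm analysed (150 per NICU) | 89.5% | 82.4% |
| Difference 15% of 42.46 = 6.37 | 91.1% | 84.5% |
| One-sided 5% (excluded by the plan) | 92.9% | 89.4% |
| ICC 0.004 | 90.1% | 83.3% |

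No two-sided row reaches 90% on 10 df.

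**7. If the pairs are analysed (5 df).** Between-NICU variance is 0.005 × 900 = 4.5, and within-NICU variance of a NICU mean is 0.995 × 900/135 = 6.63. If matching removes a share g of the 4.5, the variance of the treatment difference is 2 × [4.5(1 − g) + 6.63]/6. The article gives no value for g, so it is assumed here.

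| g | Power, t on 5 df |
|---|---|
| 0 | 70% |
| 0.5 | 79% |
| 0.8 | 85% |
| 1 | 89% |

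**8. Unequal NICU sizes.** The design effect becomes 1 + [(1 + CV²) × 135 − 1] × 0.005. The article gives no sizes, so the CV is also assumed.

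| CV | Normal | t, 10 df |
|---|---|---|
| 0.3 | 86.4% | 78.7% |
| 0.5 | 84.3% | 76.3% |
| 0.65 | 82.1% | 73.7% |

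**The case against.** The strongest defence is that the arithmetic gap is small: 87.6% against 90%, or 2.4 points. That is right. Most of the fall, to 80%, comes from the choice of reference distribution, and a reader should keep the two apart.

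The other defences of the 90% do not rescue it. Enrolling 150 per NICU is meant to cover the planned drop-out, and even with no drop-out power is 89.5%. A difference of 6.37 is not the one stated and still gives only 84.5% on 10 df. A one-sided test is ruled out by the Statistical analysis section.

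Some stronger inferences are tempting, and the article does not support them:

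- **That the ICC is misprinted and 0.004 was used.** It fits, but so does a rounded difference of about 6.24. Nothing printed separates the two.
- **That the authors used normal critical values.** No formula is given, so this is a guess. What can be said is that neither the normal nor the t calculation gives 90% with the printed inputs and a two-sided test.
- **That true power is about 70%, or the risk of a miss is 20 to 30%.** The 70% belongs to a paired t-test with no gain from matching. The article plans no paired t-test, and it matches on MOM feeding proportion, which is the outcome measure at baseline. The planned adjustment for infant and NICU characteristics could also recover some power, at some cost in degrees of freedom.
- **That NICU sizes were assumed equal, with a known loss.** The article speaks of an average of 135 and gives no spread. The direction of the effect is clear, but its size is an assumption.

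**Conclusion.** The stated 90% is wrong as written. With the printed inputs and a two-sided 5% test, power for a 6-point difference is 87.6% on a normal approximation and about 80% on 10 df. On the normal approximation, 90% needs about 155 evaluable infants per NICU where 135 are planned.

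The first figure rests only on the printed inputs and the usual design effect. The second also assumes an unmatched comparison of equal-sized NICUs, with no gain from covariates; matching or adjustment could raise it, and unequal sizes would lower it. Which input produced the printed 135 cannot be settled from the article.

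The error concerns the claim made for the design. It does not bias the effect estimate or alter the type I error of the planned analysis.

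**What to change.** Keep the 12 NICUs and about 1,800 infants, and rewrite the sample size paragraph:

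1. State the exact difference (unrounded), SD, ICC and formula that led to 135 per NICU.
2. Restate power for 6 points as about 88% (normal approximation) or about 80% (t, 10 df), or state that the design has 90% power for about 7 points (t, 10 df).
3. If the pairs will be analysed, give the 5-df power together with the assumed gain from matching: about 70% with none, up to about 89% if matching removed all between-NICU variance.
4. Show unequal NICU sizes as a sensitivity range, using the units' own admission numbers if available. At an assumed CV of 0.5, power is about 84% (normal) or 76% (t, 10 df).

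This costs one paragraph and no change in conduct. The downside is that the stated power becomes less favourable.

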Our study will have several limitations. The participating units of this study are distributed throughout all parts of Jiangsu Province. Although they can represent the situation of all regions, there may be some regional biases due to the different management modes of NICUs. Therefore, in the early stage of this study, we will obtain baseline data to account for differences due to different NICU policies. Considering that this study is randomized to different units, some patient potential confounding factors, such as gestational age, birth weight, and treatment level, cannot be completely controlled. To reduce the possible deviation between the two groups, multilevel models will be used to compare the primary outcome indicators of the two groups, and these potential confounding factors will be adjusted in the analysis stage.

The goal of our study is to improve the MOM feeding of premature infants during NICU hospitalization using WeChat mini-programs to provide lactation consultation intervention and evaluate the effectiveness of WeChat mini-programs so that it can be promoted nationwide in the future and more premature infants can benefit from it.

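### The planning ICC of 0.005 is in strong tension with the protocol's own account of how NICUs differ, the stated 90% power is not reached even at that value, and power falls quickly if the effective ICC is higher

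*Protocol article*

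**What the plan says.** The protocol article, Sample size calculation, builds the trial size on these inputs:

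- Baseline: "According to the baseline data reported (unpublished data) by each unit in 2019, the average proportion of MOM feeding was 42.46" per cent. No spread between units is given.
- Expected effect: the proportion is expected "to increase by at least 15% in the intervention group compared with that in the control group". The power statement itself is for "a difference between the group means of at least 6".
- Variability: "the standard deviation of subjects is 30.00", "assuming the intracluster correlation coefficient is 0.005". Two external references are cited for the ICC.
- Result: "We will achieve 90% power", with 1620 infants in total, 810 per arm and 135 per NICU. This is raised to 900 per arm for 10% drop-out.

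Other sections treat differences between units as important. The Background says that "a large gap persists in different regions and neonatal intensive care units (NICUs) for MOM feeding of preterm infants", and that feeding measures in each NICU directly affect milk expression and whether infants can receive MOM. Study design and Randomization pair the 12 NICUs on MOM level as well as on size. Statistical analysis lists the NICU's rate of MOM feeding as an adjustment variable. The limitations in the Discussion foresee possible regional bias from different management modes, and say "we will obtain baseline data to account for differences due to different NICU policies".

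**The concern.** The ICC is the share of total variance that lies between NICUs. A value of 0.005 says that NICUs hardly differ in MOM share once infant-level variation is set aside. That is hard to reconcile with a design that pairs and adjusts for MOM level because NICUs are expected to differ. The 2019 unit data would have informed this assumption, but the sample size section takes only their average from them.

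With six clusters per arm, the ICC largely determines precision, and adding infants within NICUs helps little. If 0.005 is too low, the trial could miss an effect of the size it was planned for, and a null result could be misread as evidence that the mini-program does not work.

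**Working it through.** **Inputs.** From Sample size calculation: difference 6 points, SD 30 (taken as the total SD), ICC 0.005, m = 135 infants per NICU. From Study design: k = 6 NICUs per arm. From Statistical analysis: two-sided alpha 0.05.

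**1. What ICC 0.005 means.** Between-NICU SD = 30 × √0.005 = 2.12 points. Around the 2019 average, 95% of true unit means would lie in 42.46 ± 1.96 × 2.12, that is 38.3% to 46.6%.

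**2. The plan's own figure.** Without clustering, n per arm = 2 × (1.960 + 1.282)² × 30² / 6² = 525.4, rounded up to 526.

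- Design effect at m = 135: 1 + 134 × 0.005 = 1.67. Required n = 525.4 × 1.67 = 877 per arm.
- Solving for m with k fixed at 6: n = 6 × 525.4 × 0.995 / (6 − 525.4 × 0.005) = 930 per arm, or 155 per NICU.

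The stated 810 does not reproduce from the stated inputs. It is approached with an ICC of 0.004 (805 to 807) or a difference of 6.25 points (about 808), neither of which is stated.

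**3. Power at 6 × 135 per arm.** SE = 30 × √(2 × DE / 810). At ICC 0.005, SE = 30 × √(2 × 1.67 / 810) = 1.926 and 6 / 1.926 = 3.11. Power is:

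- 87.6% by the normal approximation;
- 80.1% by a t test with 10 degrees of freedom (12 clusters, two arms);
- 70.4% with 5 degrees of freedom (six pairs).

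If all 900 per arm were analysed (m = 150), normal power would be 89.5%, but that uses up the drop-out allowance.

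**4. Other values of the effective ICC.** These are assumptions; the document gives no between-unit spread.

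| Effective ICC | Between-NICU SD | DE | SE | Power, normal | Power, 10 df |
|---|---|---|---|---|---|
| 0.005 | 2.1 | 1.67 | 1.93 | 88% | 80% |
| 0.01 | 3.0 | 2.34 | 2.28 | 75% | 66% |
| 0.02 | 4.2 | 3.68 | 2.86 | 56% | 48% |
| 0.05 | 6.7 | 7.70 | 4.14 | 31% | 26% |

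As m grows without limit, SE tends to 30 × √(2 × ICC / 6). Normal power is then capped at 69% for ICC 0.02 and 34% for ICC 0.05, whatever the number of infants per NICU.

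**5. What matching can recover.** Suppose pairing removes 70% of the between-unit variance (an assumption). Then SE = √(2 × (0.3 × 900 × ICC + 900 × (1 − ICC) / 135) / 6).

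| Raw ICC | SE | Power, normal | 10 df | 5 df |
|---|---|---|---|---|
| 0.02 | 1.99 | 85% | 77% | 67% |
| 0.05 | 2.57 | 65% | 56% | 47% |

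**6. What 0.005 would need as a residual.** The share of between-unit variance to be removed is 1 − 0.005 / raw ICC: 75% if the raw ICC is 0.02, and 90% if it is 0.05.

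**The case against.** The strongest reply is that the relevant ICC is the residual one. The protocol pairs units on MOM level and adjusts for the NICU's MOM rate, and both reduce it. This stands in part: step 5 shows a material recovery, and the unmatched rows in step 4 apply only if the stated ICC is what remains after matching and adjustment. But nothing in the article presents 0.005 as such a residual. The cited references cannot be seen here, so whether they support a raw or an adjusted value is unknown. A paired analysis also leaves only 5 degrees of freedom.

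A reader might infer that the protocol flatly contradicts itself. The text does not support that. The sentence on the large gap concerns NICUs and regions in general, not these 12 units in one province. The limitation on management modes is worded as a possibility. No section reports the spread among the participating units.

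The 15% could be read as 15 absolute points, and normal power at ICC 0.05 would then be about 95%. But the power statement is explicitly for 6 points, which fits a relative increase: 0.15 × 42.46 = 6.37. At 6.37 points, normal power at ICC 0.005 is 91%, so a little of the shortfall may come from rounding. With 10 degrees of freedom it is still only about 85%.

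Finally, the article does not say that infant-level 2019 records are in hand, and an ICC estimated from 12 units will be imprecise. The fix allows for both.

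**Conclusion.** The concern holds as strong tension between the ICC and the rest of the protocol, and as high sensitivity of power to that ICC. Two parts differ in certainty.

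- **Firm.** From the plan's own inputs, 810 infants per arm give 88% power by the normal approximation, 80% with 10 degrees of freedom and 70% with 5. The stated 90% is not reached.
- **Conditional.** Doubling the effective ICC to 0.01 costs about 13 points of normal power, and 0.02 leaves roughly a coin-flip. Where the trial lies depends on an ICC that the document does not give and on how much variance matching and adjustment remove.

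It is tempting to conclude that true power is far below 90%. The document does not establish that. With a raw ICC of 0.02 and 70% of between-unit variance removed, normal power would be 85%.

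The calculations assume equal cluster sizes and that 30 is the total SD.

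**What to change.** 1. Estimate the between-NICU variance of MOM share, raw and within matched pair, from the 2019 data that each unit reported. Use infant-level data if available and unit means otherwise. Report the uncertainty of the estimate.
2. Replace the 90% statement with power and detectable difference at the fixed enrolment, using small-cluster degrees of freedom (10 unpaired, 5 paired) and a sensitivity range of ICCs. Say whether the ICC used is raw or residual.
3. Keep the adjustment for the NICU's MOM rate already listed in Statistical analysis. Specify that it uses the pre-trial (2019) value and belongs to the primary model.

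The cost is a few hours of analysis and a less favourable stated power. No extra enrolment is needed, and the restatement can be made while the trial is in its main stage.

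### The stated 90% power is 87.6% on the protocol's own inputs even with 12 equal NICUs, and it makes no allowance for the differences in NICU size that the protocol acknowledges

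*Protocol article*

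**What the plan says.** The Sample size calculation section of the protocol article states: "We will achieve 90% power to detect a difference between the group means of at least 6". It adds that "the standard deviation of subjects is 30.00" and assumes an intracluster correlation of 0.005. The result is "We estimate a total sample size of 1620 (810 in the intervention group and an average of 135 in each group". Here 135 is 1620 divided by 12 NICUs. A 10% drop-out allowance raises 810 to 900 per arm. On recruitment the section says "To achieve this sample size, we will conduct a 1-year study in 12 NICUs".

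The Statistical analysis section fixes the error rate: "All statistical tests will be two-tailed", and P "< 0.05 will be considered significant".

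Three sections treat NICU size as something that varies:
- Randomization explains the matching in these words: "due to the randomization of groups as units and differences in NICU scale, a whole-group matching design will be adopted".
- Study design pairs units on number of premature infants and on scale, among other things.
- Statistical analysis lists among its adjustment variables "NICU characteristics (number of preterm infants admitted and rate of MOM feeding".

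For the primary comparison, Statistical analysis names both a cluster-adjusted chi-square and a two-level regression. The Discussion refers to multilevel models.

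**The concern.** In a cluster trial, power depends on the spread of cluster sizes as well as on their mean. The sample size paragraph lists a difference, an SD, an intracluster correlation and a mean size. None of these describes the spread, although the protocol allows for unequal size in both its randomization and its analysis.

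Pairing does not fill the gap. Two NICUs of similar size in a pair make the arms alike in size, but a pair of large units and a pair of small units still contribute unequal clusters within each arm. That inequality inflates the variance of the treatment comparison.

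If the stated power is too high, a non-significant result would be read as stronger evidence against a 6-point benefit than the design supports.

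**Working it through.** **Inputs from the protocol.** Difference 6, SD 30, intracluster correlation (ICC) 0.005, 6 NICUs per arm, mean size m = 135, 810 per arm (Sample size calculation); two-sided 5% (Statistical analysis). **Assumed:** the CV of NICU size, shown from 0 to 0.8. All powers below use the normal approximation.

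**Step 1: the stated figure, with equal NICUs.**
- Design effect = 1 + (135 − 1) × 0.005 = 1.67.
- Effective n per arm = 810 / 1.67 = 485.0.
- Standard error = 30 × √(2 / 485.0) = 1.926.
- z = 6 / 1.926 = 3.115. Power = Φ(3.115 − 1.960) = 87.6%.

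The stated 90% is therefore missed by 2.4 points. In terms of sample size, 2 × (30 × 3.2415 / 6)² = 525.4 per arm before clustering, and × 1.67 gives about 878, against 810 printed. That holds the mean size at 135. With six NICUs per arm fixed, the mean size would have to rise to about 155, or 930 per arm. The 900 to be enrolled is 810 / 0.9, so it covers drop-out and is not spare power.

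**Step 2: unequal NICUs.** Two formulas bracket the planned analyses.
- Size-weighted comparison: design effect = 1 + ((1 + CV²) × 135 − 1) × 0.005. At CV 0.4 this is 1 + (156.6 − 1) × 0.005 = 1.778, giving z = 3.018 and power 85.5%.
- Mixed-model weights: multiply the effective n by 1 − CV² × L × (1 − L), with L = 135 × 0.005 / 1.67 = 0.404. At CV 0.4 the factor is 0.961, giving power 86.3%.

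| CV of NICU size | Power, mixed-model weights | Power, size-weighted | Loss from unequal size alone (points) |
|---|---|---|---|
| 0 | 87.6% | 87.6% | 0 |
| 0.2 | 87.3% | 87.1% | 0.3 to 0.5 |
| 0.4 | 86.3% | 85.5% | 1.3 to 2.1 |
| 0.65 | 83.9% | 82.1% | 3.7 to 5.5 |
| 0.8 | 81.7% | 79.3% | 5.9 to 8.3 |

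**Step 3: check with explicit sizes.** Take illustrative pairs of 60, 90, 120, 150, 180 and 210 infants per NICU (sum 810 per arm, CV 0.38), so that both arms are perfectly balanced in size. Power is 86.4% with mixed-model weights and 85.7% size-weighted. Perfect matching on size within pairs does not restore 87.6%.

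**Step 4: detectable difference.** At 90% power this is 3.2415 × the standard error. It is 3.2415 × 1.926 = 6.24 for equal NICUs and, at CV 0.4, 6.24 / √0.961 = 6.37 with mixed-model weights or 6.24 × √(1.778 / 1.67) = 6.44 size-weighted.

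**The case against.** The strongest reply is that the effect is small and its size is assumed. No CV, unit count or unit size appears in the article. A remark about differing scale supports a CV above 0 but not a CV of 0.5 or more, and at CV 0.2 the loss is half a point or less. This stands, and it is why the result is given as a range.

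A reader might go further in several ways that the document does not support:
- *That the protocol plans for 135 infants in every NICU.* It gives 135 as an average. Equal size is only implicit in a calculation with no term for spread.
- *That the absence of a per-unit quota proves unequal enrolment.* A condensed article commonly leaves site targets to the full protocol, so nothing can rest on that silence.
- *That unequal size costs 5 points or more from a CV of about 0.45.* That counts the 2.4-point equal-cluster shortfall and uses size weighting only. At CV 0.45 with size weighting, power falls from 87.6% to 85.0%, so 2.6 points are due to unequal size. The multilevel model, which is also planned, loses less.
- *That power is nearer 70 to 80%.* Figures in that region come from a t reference with 10 degrees of freedom (80.1% even for equal NICUs). That is a separate small-cluster issue.

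Two further replies deserve mention. If the difference were 15% of the 42.46% baseline, 6.37 rather than 6, equal NICUs would give 91.1%, and 90% would survive a CV of about 0.32 (size-weighted) or 0.40 (mixed-model). But the printed difference is 6. Pairing on feeding rate and covariate adjustment may also recover some precision. The article does not quantify this or claim it in the power statement.

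**Conclusion.** The point holds in a limited form. The stated 90% does not follow from the stated inputs: it is 87.6% with 12 equal NICUs. There is therefore no reserve to absorb the size differences that the protocol acknowledges, and matching does not remove those between pairs. Any CV above 0 lowers power further, by roughly 1 to 2 points at CV 0.4 and 4 to 5.5 at CV 0.65, on top of the 2.4 points.

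These figures rest on the printed difference, SD and ICC, on an assumed CV, and on the normal approximation. At an ICC as low as 0.005 the penalty for unequal size is modest. The point is that a recalculation correcting only the equal-cluster figure would still be too high. It does not show that the trial is badly underpowered or that it must enrol more infants.

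**What to change.** In the Sample size calculation section:
1. Correct the equal-cluster figure.
2. Count eligible infants per NICU in 2019 and state the CV. The units have reported 2019 baseline data and are paired on number of premature infants, so the counts should be available.
3. Apply the allowance that matches the primary analysis: relative efficiency 1 − CV² × L × (1 − L) for the multilevel model, or design effect 1 + ((1 + CV²) × m − 1) × ICC for a size-weighted comparison.
4. Restate the power for 6 points, or the difference detectable with 90% power, at 810 evaluable infants per arm.

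The cost is one recalculation and a less favourable power statement. No change to enrolment or procedures is needed.
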